### Concealment mechanism {16b}

The allocation sequence will be implemented into, and concealed within, REDCap’s internet-based randomisation application [45].

### Implementation {16c}

An independent statistician from Clinical Studies Sweden—Forum South [46] will generate the allocation sequence. A limited number of attending infectious disease physicians at each site will be able to enrol participants and assign interventions in REDCap’s randomisation application where the allocation sequence is concealed.

## Assignment of interventions: blinding

### Who will be blinded {17a}

Trial participants and in-patient care providers will not be blinded to interventions in this pragmatic trial. Neither will the treating physician who assesses secondary endpoints 2-8. However, the central outcome assessor of the primary outcome will be blinded to interventions, as will the trial investigators, data analysts and author group. When data is extracted from the REDCap database, the allocation will be coded as “1” and “2” and the Code Key will only be revealed after statistical evaluation of the primary and secondary endpoints.

### Procedure for unblinding if needed {17b}

Because care providers and patients are not blinded, there is no reason to unblind for safety of care. The Data Monitoring Committee (DMC) will be able to unblind the database if there are clearly more reports of possibly or probably study drug-related serious adverse events than expected.

## Data collection and management

### Plans for assessment and collection of outcomes {18a}

Baseline data and allocation will be entered into the REDCap database using a short and study-specific electronic case report form (eCRF) directly when assessing eligibility and assigning allocation by the physician who recruited the participant. The trial investigators will instruct a limited number of physicians at participating centre how to access and fill out the eCRF and provide a step-by-step guide and contact information for technical assistance. The primary outcome and the secondary outcomes 2-4 will be assessed using a semi-structured interview with a trial-specific guideline and entered into a separate part of the REDCap eCRF. The first 10 participants’ interview responses will be checked for conformity between at least two study nurses. The remaining secondary outcomes will be assessed retrospectively through medical chart review and from microbiological results by the recruiting physician at 30–60 days after the patient was allocated and then entered into a final separate part of the eCRF. The retrospective chart review will also serve as a sensitivity analysis to the telephone interview for the primary outcome and the secondary outcomes of early drug discontinuation and further antibiotic prescription. A copy of the REDCap eCRF (English) and semi-structured interview guideline (Swedish) can be sent on request.

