### Strategies to improve adherence to interventions {11c}

Intervention adherence while in hospital will be monitored by the treating physician and any deviance will be required to be registered in the electronic case report form (eCRF). After patients are dismissed, the allocation-blinded outcome-assessor (the research nurse) will ask the participant whether he or she has taken all the medicines as prescribed, if not why, and how the participant perceived the treatment tolerability, and if any he or she have received any further antibiotic prescriptions for UTI since recruitment to the trial. Even though this pragmatic monitoring cannot guarantee adherence with certainty, it is similar to the how the medications would be used in the clinic. The recruiting physician will further validate that the participants have collected their study drug prescription, and that they have not received any further prescriptions, during the retrospective medical journal review.

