### Outcomes [12]

#### Primary outcome

Clinical cure 10 days (+/− 2 days, i.e. weekends) after antibiotic treatment completion defined as being alive with absence of fever (≥ 38.3 °C) and resolution of, or return to non-infected baseline of, urinary tract symptoms (as defined in inclusion criteria) without hospital readmission (for UTI symptoms) or additional antibiotic treatment (for UTI symptoms) based on a structured telephone interview performed by a centralised allocation-blinded study nurse.

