#### Secondary outcomes

Participants’ perception of treatment tolerability on a 1–10 scale.Early study drug discontinuation.Additional antibiotic subscriptions (for UTI) within 28 days from randomisation.Proportion of patients re-admitted to hospital (due to UTI symptoms) within 28 days from randomisation.Drug-related serious adverse events within 28 days from randomisation.All-cause mortality within 28 days from randomisation.Growth of EPE (phenotypically same species) in urine culture (10^3^ CFU/mL) 10 +/− 2 days after antibiotic treatment.Growth of EPE or carbapenemase-producing bacteria in faecal cultures 10 +/− 2 days after antibiotic treatment.

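### Two 28-day secondary outcomes are assigned to a telephone call held before day 28, with no rule for events found only in the chart and conflicting statements on who assesses outcomes 1–4

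*Protocol article*

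**What the plan says.** All references are to the protocol article. Numbered in listed order, the secondary outcomes are: 1 tolerability as rated by the participant, 2 early discontinuation, 3 further antibiotics, 4 re-admission, 5 drug-related serious adverse events, 6 death, 7 urine culture, 8 faecal culture.

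- **Source of outcomes 2–4.** Plans for assessment and collection of outcomes {18a}: "The primary outcome and the secondary outcomes 2-4 will be assessed using a semi-structured interview with a trial-specific guideline". Strategies to improve adherence {11c} identifies the interviewer: "the allocation-blinded outcome-assessor (the research nurse) will ask the participant whether he or she has taken all the medicines as prescribed".
- **Source of the others.** {18a} continues: "The remaining secondary outcomes will be assessed retrospectively through medical chart review and from microbiological results by the recruiting physician at 30–60 days". It then gives the chart review the role of a sensitivity analysis for the primary outcome, discontinuation and further antibiotics. It does not name re-admission there.
- **Blinding.** Who will be blinded {17a}, on those not blinded: "Neither will the treating physician who assesses secondary endpoints 2-8".
- **Tolerability.** In {11c} the nurse also asks "how the participant perceived the treatment tolerability".
- **Windows.** Outcome 3 is "Additional antibiotic subscriptions (for UTI) within 28 days from randomisation", and outcome 4 has the same window. The call follows the primary outcome: "Clinical cure 10 days (+/− 2 days, i.e. weekends) after antibiotic treatment completion".
- **Later check.** Data management {19} has the treating physician compare the primary outcome and secondary outcomes 2–4 with the medical record 30–60 days after randomisation. {11c} has the recruiting physician look for further prescriptions at the same review.

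**The concern.** Three things do not fit together.

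First, the interview is named as the assessment for two outcomes whose window is still open when the call is made. The second source that could close the gap is ranked below it for outcome 3 and given no analytic role for outcome 4 beyond a double-check.

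Second, two sections name different assessors for outcomes 2–4, one blinded and one not. Participants and care providers know the allocation, so a reader of the results needs to know which applies. Outcome 2 is also one of the three safety parameters at the interim analysis ({21b}).

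Third, by its numbering {18a} sends a participant-reported 1–10 score to chart review, which would not normally contain it.

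What is at stake is which events count in outcomes 3 and 4, and whether they can be described as assessed blind. If this stays open, the source could be chosen after the data are seen.

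**Working it through.** No stated figure has to be reproduced here. The check is day arithmetic and a side-by-side reading.

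**Day of the call**

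Inputs:
- 1–5 intravenous days before randomisation (Eligibility criteria {10}).
- A planned course of 10 days, or 7 days for ciprofloxacin in women (Treatment duration {6b}; Intervention description {11a}).
- A call 8–12 days after the end of treatment (Primary outcome {12}).

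The text available does not settle whether the intravenous days count toward the course, so both readings are used:

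- Counted: call day = course − intravenous days + (8 to 12)
- Not counted: call day = course + (8 to 12)

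| Course | Intravenous days | Earliest call | Latest call | Days left to day 28 |
|---|---|---|---|---|
| 10 days | counted | 10 − 5 + 8 = 13 | 10 − 1 + 12 = 21 | 7–15 |
| 10 days | not counted | 10 + 8 = 18 | 10 + 12 = 22 | 6–10 |
| 7 days | counted | 7 − 5 + 8 = 10 | 7 − 1 + 12 = 18 | 10–18 |
| 7 days | not counted | 7 + 8 = 15 | 7 + 12 = 19 | 9–13 |

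Over all readings the call falls on day 10–22. The interview therefore leaves 28 − 22 = 6 to 28 − 10 = 18 days unseen, or 6/28 = 21% to 18/28 = 64% of the window.

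**Difference between arms**

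Only women on ciprofloxacin have a shorter planned course, by 10 − 7 = 3 days. Table 1 expects about 25% of controls on ciprofloxacin. The mean shift in the control arm is at most 0.25 × 3 = 0.75 day if all of them were women. It is about 0.4 day if half were; that share is an assumption, because no sex split is given.

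**Do chart-only events count?**

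- {19}: the chart is a double-check of outcomes 2–4. What happens when the two differ is not stated.
- {18a}: the chart is a sensitivity analysis for outcomes 2 and 3; outcome 4 is not named.
- {20a}: a discrepancy between the sources is resolved as failure, but the rule is written for the primary outcome.
- Table 3 footnote: a similar rule in general terms. The table itself is not shown, so the rows it applies to cannot be seen.
- {18b}: for participants not reached by telephone, only 28-day mortality is named as recoverable from the chart.

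None of these states that a re-admission or prescription found only in the chart enters the main analysis of outcome 3 or 4.

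**Who assesses what?**

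| Outcome | {11c} | {17a} | {18a} |
|---|---|---|---|
| 1 | blinded nurse asks | not on the physician's list | chart review, by numbering |
| 2 | blinded nurse asks | unblinded physician | interview |
| 3 | blinded nurse asks; prescriptions checked in the chart | unblinded physician | interview |
| 4 | not mentioned | unblinded physician | interview |
| 5–8 | not mentioned | unblinded physician | chart and microbiology |

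The sections agree on 5–8 and disagree on 1–4.

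**The case against.** The strongest reply is that the two-source design already works. The physician checks outcomes 2–4 in the chart and assesses 5–8 there, which together gives the 2–8 of {17a}. Outcome 1 is missing from that list because the nurse collects it. On this reading {17a} and {18a} describe two halves of one scheme, and the only slip is the phrase that sweeps outcome 1 into chart review. The Table 3 footnote may supply the combination rule, the outcomes are exploratory ({14}), and the choice of source could be left to an analysis plan.

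Part of this stands. The reconciliation is plausible, Table 3 might list the assessors, and a numbering slip is possible, since the items in {11c} correspond to outcomes 1–3. But {17a} makes the physician the assessor of 2–4, not a checker, and {18a} goes beyond leaving the source open: it ranks the interview first and the chart as a sensitivity analysis for outcome 3. A plan that followed {18a} would use a main source that stops short of the window.

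A reader might also infer that late events are lost, and lost unequally between the arms. The documents do not support either inference. The day 30–60 review falls after day 28, applies to both arms and covers outcomes 2–4, so late events can be found. The difference in call timing is limited to 3 days in a subset of about a quarter of controls, and the chart review covers those days too.

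**Conclusion.** The point holds as a defect of source and assessor. The interview named for outcomes 3 and 4 cannot observe the last 6 to 18 days of a 28-day window. The chart review can, but the protocol does not say that its events count in the main analysis. The sections also conflict on whether outcomes 2–4 are assessed blind, and {18a} misplaces outcome 1. The documents do not show which section states the intended assessor.

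The day range assumes the planned course is completed, with randomisation after 1–5 intravenous days. It covers both readings of whether those days count, and the conclusion is the same under each. It is also subject to Table 3, which is not shown.

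This should be corrected, but it does not threaten the trial: the outcomes are exploratory, and the primary outcome, margin and sample size are unaffected.

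**What to change.** Give one source and one assessor per outcome, and align sections {11c}, {17a}, {18a} and {19}:

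- **Outcome 1:** the blinded interview.
- **Outcome 2:** the blinded interview, with the chart as a check.
- **Outcomes 3 and 4:** the day 30–60 chart and prescription review, covering randomisation to day 28 in both arms. Count an event found in either the interview or the chart, and state that the chart part is extracted by unblinded site staff.
- **Outcomes 5–8:** unchanged.

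In {18a}, replace the sensitivity-analysis label for outcome 3 accordingly and name outcome 4. In {17a}, say that outcomes 1 and 2 come from the blinded interviewer and that 3 and 4 combine a blinded and an unblinded source.

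The cost is a text amendment, because both sources are already collected. The price is an open acknowledgement that later events in outcomes 3 and 4 rest on unblinded extraction. Reporting the interview-only result alongside would let readers judge how much that matters. The change should be made before the interim and final analyses.

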### Plans to promote participant retention and complete follow-up {18b}

Since the follow-up is via telephone and done centrally, we expect that retention will be high. If the central outcome assessor cannot reach the participant, they will contact the recruiting physician who will check if the participant is deceased through the medical chart. Participants who are not reported dead and still cannot to be reached for the telephone interview follow-up will not qualify for analysis of the primary outcome or bacterial culture-related outcomes but can be assessed retrospectively from medical chart review regarding 28-day mortality, which is important for the evaluation of harm. We suspect that patients who deviate from the prescribed intervention will often be categorised as a negative outcome in the primary outcome assessment (e.g. new antibiotic prescribed), while some will simply be regarded as protocol violations. However, if a participant chooses to discontinue the trial, any collected data will be discarded, and the participant will only appear as a figure in the study flow chart.

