## Sample size {14}

We expect a clinical cure rate of 93%, based on previous trials on antibiotic efficacy in febrile UTI exploring similar primary outcomes [37, 41]. We have chosen a classic absolute non-inferiority margin of 10% in accordance with the U.S. Food and Drug Administrations (FDAs) recommendation on developing new drugs for complicated UTIs [43]. We consider this to be suitable considering the low severity of all aspects of the composite primary endpoint except for 28-day mortality which we will evaluate specifically as a secondary endpoint and in the interim analysis. When using a one-sided alpha of 2.5% and performing a statistical simulation of 300 enrolled patients in 30 clinics with an intraclass correlation coefficient of 0.1 and generalised estimated equations (GEE) comparison between two groups with a random intercept for site as the primary analysis we reach 90% power. We plan on recruiting 330 patients to allow for 10% loss to follow-up. The study is not powered to infer non-inferiority between the intervention and any single antibiotic in the control group, but only towards the control group as a whole. The secondary objectives should be considered exploratory and are not based on sample size calculations.

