### Methods in analysis to handle protocol non-adherence and any statistical methods to handle missing data {20c}

We will analyse the population both as intention-to-treat (ITT, i.e. as randomised), modified intention-to-treat (mITT, i.e. patient who took at least one dose of allocated study medication) and per protocol (PP, i.e. no major protocol deviations and missed a maximum of two doses of allocated study drug). We will only state non-inferiority if all three types of analyses provide concordant results [49]. If results are discordant, it will require a close examination of the data and could lead to either a statement of conditional non-inferiority or final uncertainty by the steering committee (SC).

All variables will be screened for frequency and type of missingness (i.e. missing completely at random, missing at random or missing not at random). Multiple imputation with chained equations will be used if missingness is above 5% in any variable included in the primary or secondary analysis. In the case of missingness, data with multiple imputation will be regarded as the primary analysis and complete case analysis will be performed as a sensitivity analysis.

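### Unreachable survivors are excluded from the primary outcome, which conflicts with the ITT and imputation rules and leaves their charted failures uncounted in the primary analysis

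*Protocol article*

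**What the plan says.** - **Retention {18b}.** If the interviewer cannot reach a participant, the recruiting physician checks the chart for death. Those not reported dead who "still cannot to be reached for the telephone interview follow-up will not qualify for analysis of the primary outcome" may still be assessed from the chart, but only 28-day mortality is named.
- **Populations and missing data {20c}.** ITT is everyone as randomised. Chained-equation imputation applies when any analysed variable is more than 5% missing, and then "data with multiple imputation will be regarded as the primary analysis and complete case analysis will be performed as a sensitivity analysis". The section also states: "All variables will be screened for frequency and type of missingness", naming the three standard mechanisms.
- **Sample size {14}.** "We plan on recruiting 330 patients to allow for 10% loss to follow-up".
- **Primary outcome [12].** Cure requires, among other things, no readmission and no additional antibiotic for UTI symptoms.
- **Chart review ({18a}, {19}).** The primary outcome is checked against the medical record 30 to 60 days after randomisation.
- **Discordance (Table 3 footnote, {20a}).** If interview and chart disagree, the patient is a failure.
- **Additional analyses {20b}.** A sensitivity analysis reports the primary outcome from chart review against the telephone interview.

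**The concern.** Leaving out everyone who was not interviewed is in effect a complete-case analysis. Section {18b} therefore makes primary what {20c} makes a sensitivity analysis. A non-inferiority trial needs one rule for its primary analysis set before the allocation is known. With two, the choice could be made after results are seen.

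The chart rule is also uneven. A charted readmission overrides a favourable interview, yet the same event in a patient who did not answer the telephone has no stated effect on the primary outcome. If such failures are more common in one arm, leaving them out shifts the risk difference. If they are more common in the PAC arm, the shift favours non-inferiority. Requiring ITT, mITT and per-protocol results to agree gives no protection, because {18b} removes these patients from all three.

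**Working it through.** **1. The plan's own figures.** Inputs from {14}: 93% cure, 10-point margin, one-sided alpha 2.5%, 300 patients in 30 clinics "with an intraclass correlation coefficient of 0.1", 90% power, 330 recruited.

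- Simple formula, 150 per arm: SE = √(2 × 0.93 × 0.07 / 150) = 0.0295. Power = Φ(0.10/0.0295 − 1.96) = 92.4%.
- Simulated GEE with identity link, ICC 0.1 and robust SE (Gaussian working variance in place of binomial), under several site and ICC variants: 90.9% to 92.8%.
- Loss: 300 × 1.10 = 330; 300/0.90 = 334. With 330 recruited, 330 × 0.90 = 297 are evaluable, and the simple formula gives 92.2%.

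The stated design reproduces, and the sample size is not in question here.

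**2. Does the conflict arise?** The allowed loss is 0.10 × 330 = 33 patients, twice the 5% trigger for imputation. On the planning figure, both rules apply to the same people. At 5% or less no imputation is promised, and the conflict is then only with ITT as randomised.

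**3. A charted UTI readmission or UTI antibiotic, by whether the patient was reached**

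| | Reached, reports cure | Not reached, alive |
|---|---|---|
| {20a}, Table 3 footnote | Failure | Rule covers two differing reports; here there is only one |
| {18b} | Not applicable | Outside the primary outcome |
| {20c}, above 5% missing | Not missing | Imputed, although the chart has settled it |
| {20b} chart-review sensitivity | Failure | Can appear as failure |

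Death is the only charted event that {18b} acts on, so deaths are not lost.

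**4. Size, under assumed rates.** The documents give no failure rate for unreachable participants. Assume 165 per arm, a fraction u unreachable in each arm, 93% cure among those reached in both arms, and 7% failure among unreachable controls. Let f be the failure rate among unreachable PAC patients. The simple formula is used, without clustering.

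- Excluded, u = 10%: n = 148.5 per arm, RD = 0, bound = −1.96 × √(2 × 0.93 × 0.07 / 148.5) = −5.8 points.
- Counted, u = 10%: PAC cure = 0.90 × 0.93 + 0.10 × (1 − f); control cure = 93%.
  - f = 30%: PAC 90.7%, RD = −2.3, bound = −2.3 − 1.96 × √((0.93 × 0.07 + 0.907 × 0.093)/165) = −8.2.
  - f = 50%: PAC 88.7%, RD = −4.3, bound = −4.3 − 1.96 × √((0.93 × 0.07 + 0.887 × 0.113)/165) = −10.5.
- Counted, u = 10%, 30% failing in both arms: RD = 0, bound −6.3.
- u = 5%: excluded −5.6 (−5.65 before rounding); counted −6.9 at f = 30% and −8.0 at f = 50%.

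**5. Error rate at the margin.** Suppose true cure is 93% against 83% and 10% per arm are excluded. PAC cure among those reached is then (0.83 − 0.10 × (1 − f))/0.90. For f = 17%, 30% and 50% this gives 83.0%, 84.4% and 86.7%. The chance of wrongly declaring non-inferiority is 2.5%, 5.9% and 18.2%. With 5% excluded it is 2.5%, 3.8% and 7.1%.

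**The case against.** The two sections can be read together: {18b} says whose outcome was not ascertained, and {20c} says what is then done about it. That would be a coherent plan, but the text does not state it. It would also still impute an outcome that the chart has already shown to be a failure.

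Other points on this side stand, and they limit what a reader might infer:

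- **That known failures vanish from the trial.** They do not. The chart-review sensitivity analysis can show them, although the non-inferiority claim does not rest on it.
- **That imputation would turn them mostly into cures.** The imputation model is not given, as is usual in an article. Chart findings could be predictors in it.
- **That all 33 allowed losses are affected.** The chart problem concerns only unreachable survivors with a charted UTI event, a number not given. At the plan's 7% failure rate, 33 patients would include about 2 failures of any kind (33 × 0.07 = 2.3).
- **That a handful of failures decides the trial.** With 150 per arm, the observed difference must be better than −0.10 + 1.96 × 0.0295 = −4.2 points, and 7/165 is 4.2 points. But 7 of about 16.5 unreachable PAC patients is 42% failing, with none in control.
- **That the bias must favour PAC.** This needs failures among the unreachable to be more common in that arm. The documents neither show nor exclude it; participants and treating physicians are unblinded {17a}.

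The chart reviewer is also unblinded. However, {20a} already lets that review overturn the blinded interview.

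**Conclusion.** The concern holds as a conflict between stated rules. Section {18b} excludes unreachable survivors. That departs from ITT as randomised and, above 5% missingness, from imputation as the primary analysis. It also leaves a charted failure component uncounted in the primary analysis for these patients alone.

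The effect on the result is conditional. With equal cure among those reached, equal failure among the unreachable creates no false difference. At 10% excluded, a 7% against 30% split costs 2.3 points and non-inferiority is still met; a 7% against 50% split costs 4.3 points and crosses the margin. At 5% excluded, neither split crosses it. These failure rates are assumptions.

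The planned screening for type of missingness is a smaller fault: observed data cannot separate missing at random from missing not at random. The lack of a tipping-point analysis is not a finding, since that is commonly left to the SAP.

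**What to change.** 1. In {18b}, delete the words that disqualify unreachable participants from the primary outcome.
2. State that an unreachable participant with a charted death, UTI readmission or additional UTI antibiotic up to the test-of-cure date is a failure.
3. State that the remaining unreachable participants are missing and handled under {20c} within the ITT set. The imputation model should include arm and the chart-review findings. Otherwise chart-negative patients are imputed at a failure rate that already contains the charted failures.
4. Keep complete case and the chart-based outcome as sensitivity analyses.
5. In {20c}, drop the claim that screening identifies the type of missingness. As a recommendation for the SAP, add a delta-adjusted sensitivity analysis.

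The cost is revised wording and a little more analysis. The chart data are already collected and the sample size does not change. The downside is more reliance on an unblinded chart review, which {20a} already accepts for patients who were reached.

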### Plans for collection, laboratory evaluation and storage of biological specimens for genetic or molecular analysis in this trial/future use {33}

Post-treatment urine and rectal specimens will be financed by the trial but sent to each participating centre’s microbiological laboratory and will be evaluated as per clinical routine and susceptibility testing according to EUCAST guidelines. Only culture positive findings of EPE are noted, and samples will be discarded after 2 weeks from collection without further analysis. Isolates from original urine and blood samples collected from participants at the coordinating microbiology centre (Lund) will be saved in the microbiology department’s freezer storage for preliminary future study of PAC MIC.

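### Participants not reached by telephone are barred from the urine and faecal culture outcomes, although those outcomes come from the laboratory and not from the interview

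*Protocol article*

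**What the plan says.** The rule is in the protocol article, section {18b} on retention. "Participants who are not reported dead and still cannot to be reached for the telephone interview follow-up" are the group concerned, and they "will not qualify for analysis of the primary outcome or bacterial culture-related outcomes". The same sentence keeps them for one outcome: they "can be assessed retrospectively from medical chart review regarding 28-day mortality".

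Section {18a} describes where each outcome comes from. "The primary outcome and the secondary outcomes 2-4 will be assessed using a semi-structured interview". The others, which include the two culture outcomes, are "assessed retrospectively through medical chart review and from microbiological results by the recruiting physician at 30–60 days after the patient was allocated". Section {33} adds the route of the specimens: "Post-treatment urine and rectal specimens will be financed by the trial but sent to each participating" centre's own microbiology laboratory, where they are processed as in clinical routine.

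Section {20c} defines intention-to-treat as analysis as randomised and sets the missing-data rule: "Multiple imputation with chained equations will be used if missingness is above 5% in any variable included in the primary or secondary analysis". In that case the imputed analysis is the primary one and the complete-case analysis is a sensitivity analysis.

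**The concern.** The culture outcomes do not need the interview as a data source, yet being reached by telephone is a condition for entering their analysis. If an unreached participant did return a trial specimen, a measured result is set aside for a reason unrelated to whether it was measured.

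Two things are at stake. First, inclusion depends on an event after randomisation in a trial where participants know their treatment, so the analysed groups need not stay comparable. Second, the Discussion (Methodology) gives microbiological cure a cross-checking role: a substantial discrepancy from clinical cure is to be investigated. That check is weaker if both outcomes go missing for the same people for the same reason.

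**Working it through.** **1. Source of the outcome against handling when not reached**

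| Outcome | Source, {18a} | If alive and not reached, {18b} |
|---|---|---|
| Primary, clinical cure | Interview | Barred |
| Secondary 6, 28-day mortality | Chart review at 30–60 days | Kept |
| Secondary 7 and 8, cultures | Microbiological results, collected at the same 30–60 day review | Barred |

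The bar follows from the data source for the primary outcome. It does not for the cultures, which the same physician collects at the same review as the mortality outcome that is kept. No text shown makes a culture result depend on a completed interview.

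**2. The plan's own figures**

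The Sample size section states 90% power with 300 patients, and 330 recruited for 10% loss.

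- Loss: 300 × 1.10 = 330. Dividing instead, 300 / 0.90 = 333.3, so 334. The two agree closely.
- Power, closed form, 93% in both arms, margin 10 points, one-sided 2.5%: SE = √(2 × 0.93 × 0.07 / 150) = 0.0295; 0.10 / 0.0295 − 1.96 = 1.43; power 92.4%.
- Power by simulation, 30 sites of 10, intraclass correlation 0.1, cluster-robust standard error, no sex term: 90.7% with simple randomisation.

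These figures reproduce. They concern the primary outcome and do not depend on this point.

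**3. How many could be barred, and how many results that could cost**

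If the whole allowance were non-contact among living participants: 0.10 × 330 = 33 barred, 297 left. The documents do not give the share of the 33 with a trial specimen, so the full range is shown:

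| Share with a specimen (assumed) | Results left out, per specimen type |
|---|---|
| 0% | 0 |
| 25% | about 8 |
| 50% | 16–17 |
| 75% | about 25 |
| 100% | 33 |

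At 5% non-contact the range is 0 to 16–17; at 2% it is 0 to about 7.

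**4. The imputation trigger**

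5% of 330 is 16.5, so 17 or more missing values pass it. At 33 barred, missingness is 33 / 330 = 10%, and imputation becomes the primary version for that outcome.

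**5. Precision**

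Half-width of the 95% interval for a risk difference, equal arms, ignoring clustering: 1.96 × √(2p(1 − p) / (N/2)).

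| Prevalence p (assumed) | N = 297 | N = 330 |
|---|---|---|
| 10% | 6.8 points | 6.5 points |
| 30% | 10.4 points | 9.9 points |
| 50% | 11.4 points | 10.8 points |

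The loss of precision is small even if all 33 had specimens.

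**6. Selection**

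The planned estimate is a between-arm risk difference. Leaving out the unreached shifts it by w × (difference among the unreached − difference among the reached), where w is the unreached share of all participants with a specimen.

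- All 33 have specimens: w = 33 / 330 = 0.10. A gap of 10 to 30 points (assumed) gives a shift of 1 to 3 points.
- Half have specimens, and all 297 reached participants do: w = 16.5 / 313.5 = 0.053. The same gaps give 0.5 to 1.6 points.
- None have specimens: no shift.

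**The case against.** The strongest reply is that the sentence may only record a fact of logistics. Sections {18a} and {33} say who collects the results and which laboratory processes the specimens, but not how a discharged participant is asked for one. The cultures and the interview share the same 10 +/- 2 day window. The Trial status section shows that version 5.0 replaced a live visit by the telephone interview, and that version 5.1, a week later, updated microbiological sampling. The Discussion notes that follow-up urine cultures are outside Swedish routine. If the call prompts the specimen, an unreached participant will rarely have one. The participant timeline (Table 3) could settle this, but it is not shown. This objection stands against any claim about size. It does not rescue the wording, which states who qualifies for analysis rather than who is expected to have data.

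A second objection concerns the remedy. Admitting every culture found in the window would bring in cultures taken because a patient had symptoms, while well participants who were not reached stayed missing. Ascertainment would then depend on outcome. This stands, and the fix has to be limited to scheduled specimens.

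Third, no text says that a recorded culture value is deleted and then imputed. Imputation of an observed result follows only if the bar in {18b} is read as making the value missing under {20c}. That is a possible reading, not a stated one.

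**Conclusion.** The point holds as a badly fixed analysis rule of minor consequence. Section {18b} makes telephone contact a condition for two outcomes that do not come from the telephone interview. Any trial specimen from an unreached living participant would be left out and might be imputed. The number is unknown: 0 to 33 of 330 if the whole 10% allowance is non-contact, and near 0 if the call prompts sampling. The shifts of up to 3 points shown above rest on assumed gaps between reached and unreached participants.

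Some stronger readings are tempting but are not supported:

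- A reader might infer that observed results will certainly be lost. The documents do not show that such specimens will exist.
- A reader might infer that eradication will look better than it is, because unreached people with cultures are back in care. With assumed growth of 50% in the 5% of the sample left out with specimens and 25% in the 90% reached, pooled growth would be (0.90 × 0.25 + 0.05 × 0.50) / 0.95 = 26.3% against 25.0%, about 1.3 points. That is a shift in pooled prevalence. With equal loss and the same pattern in both arms it cancels in the risk difference, and the direction is not established.
- A reader might take culture as the only objective efficacy measure. All-cause mortality is objective too, and faecal culture measures carriage rather than cure.

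The Sample size section calls the secondary objectives exploratory. The primary outcome, the non-inferiority conclusion and the sample size are untouched.

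**What to change.** In section {18b}, delete the reference to the culture outcomes from the sentence on participants who cannot be reached. Add one statement with three parts:

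- Every randomised participant with a protocol-scheduled post-treatment urine or faecal specimen in the 10 +/- 2 day window enters the analysis of that outcome, whether or not the interview took place.
- Only participants without such a specimen count as missing for that outcome under {20c}.
- Clinically triggered cultures are not substituted for scheduled ones in the main analysis; they may be used in a sensitivity analysis.

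The separate rule in {18b} on participants who choose to leave the trial is not altered by this.

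The cost is a short wording change. Microbiological results are already collected at the 30–60 day review, so no new specimen or visit is needed; the record only has to show whether a culture was scheduled or clinically triggered.
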